### Sampling

FCHVs will provide assistance in identifying eligible participants for the interviews. They maintain an updated list of community members served by their health facilities, including families with newborn children and record of the child’s immunization status. Using these lists, FCHVs will identify homes with potential participants for us to contact and recruit. For two of the eight focus groups, we will only recruit individuals from marginalized communities based on their caste to broaden our scope and gain a more comprehensive image of the community and their array of experiences. Each discussion group will consist of five to nine participants. For In-depth interviews, potential participants will be excluded if any member of their family has participated in one of our interviews or focus groups. Participants of the key informant interviews will be identified through discussions with community leadership.

### Instruments

We have prepared the qualitative instruments using influence from the theory of normative social behavior (
Rimal & Real, 2005) and choice architecture (
Thaler *et al.,* 2014). Interview and focus group instruments also include concepts from the literature on facilitators and barriers of immunization (
Acharya *et al.,* 2019;
Shrestha *et al.,* 2016) and adapted survey questions regarding clinic infrastructure from the Rapid Assessment Tool (
Scholz *et al.,* 2015) and the Site Assessment for Maternal and Newborn Health Programs (
JHPIEGO, 2004). The instruments were adapted for local use based on feedback from the Nepali team on cultural considerations including language, phrasing, and use of probes. The tools will undergo pre-testing and will be revised to ensure smooth flow of questions, avoid confusing technical terms and jargon, and assure appropriate phrasing to avoid misunderstanding or offense.

Topics covered in each interview and focus group will vary based on the instrument in use as well as flow of the conversation. All qualitative instruments include questions regarding facilitators, barriers, and social norms of immunization. The focus group guide will also cover the physical and social characteristics that mothers desire in an ideal health facility, a description of their current health facility, and typical communication between caregivers and health care providers. The in-depth interview guide will cover the family’s personal experiences with vaccination, family involvement in child health and decision-making, and aspirations for the child’s education and career. The key informant interview guide will include items regarding immunization coverage in the ward, typical communication between caregivers and health care providers, a physical description of the local health facility, opinions of their workload, and feasibility of the proposed intervention.

Each of these instruments will aim to reveal the facilitators of and barriers to immunization uptake across various socioecological levels. For instance, the in-depth interviews with fathers and grandmothers will address the household-level factors while the focus group discussions with mothers will get at the interpersonal and community levels. Additionally, the key-informant interviews will address the systems level variables at play.

Interview guides are available as
*Extended data* (
[name], 2020).

## Quantitative methods

Whereas the qualitative component of the research helps inform the intervention design and the quantitative instrument, the quantitative component’s primary use is in tabulating the impact of the intervention in as rigorous a manner as possible.

### Study design

We will use a clustered quasi-experimental design with panel data to measure the impact of the intervention on immunization behaviors, intent to vaccinate, and uptake of other health services. Participants from each of the six study sites will complete a baseline survey preceding intervention implementation and an end-line survey approximately eight months later. Data collectors will read questions aloud to participants and then record responses on a handheld tablet. Surveys are available as
*Extended data* (
[name], 2020).

In addition, the physical conditions of the health facilities and immunization centers will be assessed using checklists at baseline. These checklists will be used to corroborate subjective reports from interviews, focus group discussions, and surveys and assist with identifying needed resources to include in the intervention design. Our data collectors will visit each health facility and the surrounding immunization centers on the designated “Immunization Day” to complete the checklists.

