## Abstract

**Background: **Each year, 600,000 children under 5 years old die from vaccine-preventable diseases globally. Immunization is an effective way to prevent many diseases, saving two to three million lives per year. The Nepal National Government recommends vaccinations for all children for 11 diseases by 15 months of age. However, only 78% of children between 1-2 years of age have received all recommended vaccines and only 43% receive them at the age-appropriate times for which they are scheduled.

**Objectives: **This protocol describes the development of an intervention – called “Rejoice Architecture” – that is informed by three theoretical perspectives: choice architecture, the broken windows theory, and the theory of normative social behavior. We also describe a mixed-methods approach to develop the intervention, which will improve the physical and social environments of health facilities in Makwanpur, Nepal. We hypothesize this intervention will improve immunization behaviors and intentions among mothers of children younger than 2 years, pregnant women, and prospective mothers.

**Methods: **We describe the qualitative formative assessment to understand existing attitudes, norms, and behaviors among caregivers, healthcare workers, and government representatives. The formative assessment will include in-depth interviews, key informant interviews, and focus group discussions. We also describe the overall quasi-experimental study design, used to assess intervention impact.

**Impact: **This study will contribute to the social and behavioral change communication intervention research by offering a novel strategy for increasing immunization. This study will also illustrate to policymakers the value of structural change for health service delivery.

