## Introduction

 Communicable diseases constitute a global health threat, with low- and middle-income countries experiencing the greatest burden (
The World Medical Association, 2020). Each year, 1.5 million people die from vaccine-preventable diseases, 600,000 of whom are children under the age of 5 (
Gavi, 2020). Immunization is an effective way to prevent disease and save lives, with two to three million lives saved by vaccines every year (
World Health Organization, 2019). Individuals benefit from immunization through illness prevention, reduced healthcare costs, and greater productivity for themselves and their caregivers (
Gavi, 2020;
Njau & Cairns, 2016;
Ozawa *et al.,* 2012). Children, who are often at greater risk of morbidity and mortality from communicable disease, experience greater cognitive ability, physical strength, and school performance when they receive vaccines (
Gavi, 2020;
Nandi & Shet, 2020). Immunizations also contribute to improved community health through herd immunity and greater economic stability from long-term cost savings (
Fox *et al.,* 1971;
Gavi, 2020;
Ozawa *et al.,* 2012;
Ozawa *et al.,* 2017). 

Currently, nearly 20 million children worldwide younger than one year old have not received the minimum basic vaccines they need to live long, healthy lives; 77% of which represent children living in Gavi-supported countries (
Gavi, 2020). Furthermore, only 17% of children under 1 have received the full dosage recommended by the World Health Organization (
Gavi, 2020). This coverage gap is present in Nepal, where only 78% of children between 1–2 years have received all recommended vaccines (
Ministry of Health Nepal *et al.,* 2017). It is important to note, though, that while the majority of children receive their vaccines by the age of 2, only 43% receive them at the age-appropriate times for which they are scheduled (
Ministry of Health Nepal *et al.,* 2017). Moreover, immunization coverage is highly variable in Nepal, with rates ranging from 65% in some provinces to 93% in others (
Ministry of Health Nepal *et al.,* 2017). Coverage is dependent on the specific vaccine as well, ranging from 73% for the first dose of the Pneumococcal vaccine to 98% for the Bacille Calmette Guerin (BCG) vaccine (
Ministry of Health Nepal *et al.,* 2017). These data demonstrate a critical need to ensure consistent and comprehensive coverage of immunization, including in Nepal.

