### Facilitators and barriers of immunization

Studies in Nepal show that institutional delivery is a prominent facilitator of vaccine uptake (
Acharya *et al.,* 2019;
Shrestha *et al.,* 2016).
Shrestha *et al.* (2016) offer one potential reason for this, stating that the first vaccine (BCG) is often administered immediately after birth, which is more likely to be readily available in a health facility setting than at home. Furthermore, in institutions, new mothers are surrounded by numerous healthcare staff who can share their recommendations for future vaccines (
Shrestha *et al.,* 2016).

Multiple studies in Asia and Africa have found a positive association between parental knowledge of immunization and vaccine uptake (
Odusanya *et al.,* 2008;
Owino *et al.,* 2009;
Perry *et al.,* 2020). This can refer to knowledge about the purpose of vaccines, appropriate ages to receive specific vaccines, age at which a child should complete the vaccines, and symptoms of vaccines, among other topics (
Odusanya *et al.,* 2008). Some studies show that even in areas of low literacy, parental knowledge is a significant determinant of full immunization (
Matsumura *et al.,* 2005;
Odusanya *et al.,* 2008). An important aspect of parental knowledge is awareness of the vaccine schedule, which is also strongly correlated with immunization coverage (
Owino *et al.,* 2009;
Shrestha *et al.,* 2016). In Nepal, full immunization requires seven separate visits over 15 months; it is essential that parents know and remember this schedule in order to bring their children to the facility at the appropriate time (
Acharya *et al.,* 2019).

For countries like Nepal that rely on immunization cards to track children’s vaccine records, immunization card retention is a major facilitator of uptake (
Acharya *et al.,* 2019;
Perry *et al.,* 2020).
Perry *et al.* (2020) found that in Bangladesh where, like Nepal, immunization cards are required to receive vaccines, parents are met with anger, shouting, and in some cases a fee when they lose or forget their card. Improving immunization card retention has serious implications for encouraging immunization in Nepal, where the retention rate for immunization cards is only 52% (
Acharya *et al.,* 2019).

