### Participants

Eligible participants include mothers of children younger than two years, pregnant women, and prospective mothers. Prospective mothers are defined as women of reproductive age (18–30 years) who are not currently pregnant and do not have a child two years or younger, but express interest in having a child in the future. All participants must be 18 years or older and live within a one-kilometer radius of the health facility being studied. Potential participants will be excluded if they or a member of their family participated in any of the qualitative assessments.

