### Sampling

Like the qualitative methods, FCHVs from each ward will assist in identifying women in the community who fit the eligibility requirements. With their list of names and locations, data collectors will randomly select houses for recruitment. The target sample size is
*n* = 950 (treatment = 475, control = 475) with an anticipated attrition rate of 20%. This was determined by assuming an increase in vaccination rates from 83% (2019 estimate) to 93% (envisioned), an alpha level of 0.05 and power of 80%, and data collection from 6 clusters. To estimate the vaccination rate in Makwanpur in 2019, we assumed an increase of approximately 6% from 2017, when the data were last reported, based on antigen coverage trends from 2014 to 2017 (
Ministry of Health Nepal Department of Health Services, 2018). We estimate an intraclass correlation of 0.01, making the required sample size 380 in the treatment and 380 in the control groups. However, because this is a panel design, we envision an attrition rate of 20%, which brings our sample size at baseline to 950. We will sample four cohorts of women with children younger than one year, women with children between 1–2 years, women who are pregnant at baseline, and prospective mothers. We anticipate greatest availability of women in the first two cohorts, and the least availability of pregnant women, which we expect will create variation in our sample sizes between cohorts. For the complete anticipated sampling breakdown, see
Table 2.

**Table 2. T2:** Breakdown of quantitative data collection by treatment and control facilities.

Participant	Control	Treatment	Total
Women with children <1 year	150	150	300
Women with children 1–2 years	150	150	300
Pregnant women	50	50	100
Prospective mothers	125	125	250
Total	475	475	950

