### Contribution to the field

Currently in phase 2 of the study, we have collected baseline data and modified the Rejoice Architecture intervention design, and will implement the intervention when COVID-19 travel restrictions are lifted. We expect this project will make incremental, though important contributions to the global efforts in increasing immunization and reducing child mortality. The iterative and multi-phase procedure will allow for constant adaptation of the intervention, driven by a deepened understanding of individual and contextual factors that will be achieved through community-based participation at every phase. This theory-driven approach will offer a novel connection between community-level theory and individual behavior, bridged by changes in social norms. More specifically, this study will test the pathway between physical infrastructure, mothers’ behavior and child immunization, and will therefore provide direction for future research aiming to address immunization uptake and other service use in LMICs.

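### More than a third of the enrolled children may be past the 15-month schedule before the intervention starts, and the sample size makes no allowance for this in the panel-measured behaviour outcome

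*Protocol article*

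**What the plan says.** - **Schedule.** The Abstract gives the end of the schedule: "The Nepal National Government recommends vaccinations for all children for 11 diseases by 15 months of age". The section on facilitators and barriers agrees: "full immunization requires seven separate visits over 15 months".
- **Panel.** Quantitative methods, Participants: "Eligible participants include mothers of children younger than two years, pregnant women, and prospective mothers". Table 2 under Sampling plans 300 mothers with a child under one year, 300 with a child aged 1–2 years, 100 pregnant women and 250 prospective mothers, 950 in all.
- **Timing.** Study design: "Participants from each of the six study sites will complete a baseline survey preceding intervention implementation and an end-line survey approximately eight months later". Contribution to the field adds that "we have collected baseline data and modified the Rejoice Architecture intervention design, and will implement the intervention when COVID-19 travel restrictions are lifted". The length of the wait is not stated.
- **Outcome.** Under Instruments and Outcomes, immunization behaviour is a primary outcome, measured in mothers as how far the national schedule was followed. Pregnant and prospective women report intention instead. Under Data analysis, Quantitative, however, the primary hypothesis concerns newborns vaccinated as a share of live births in the catchment area.
- **Effect assumed.** Sampling uses a rise from 83% to 93%, alpha 0.05, power 80%, six clusters, an intraclass correlation of 0.01 and 20% attrition.
- **Late doses.** Introduction: "while the majority of children receive their vaccines by the age of 2, only 43% receive them at the age-appropriate times".

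**The concern.** An intervention can affect only doses given after it starts. A child already past 15 months at that point has no scheduled dose still to fall due: timeliness is fixed, and completion can improve only if a missed dose is made up. Half of the mothers with a child were recruited in the 1–2-year band, and because the panel is fixed and baseline is done, each month of waiting moves more children past the end of the schedule. The sample size nevertheless assumes that the whole group shows the full 10-point rise. If all these children are scored on their whole history, the estimated effect is pulled toward zero and an effective intervention could be reported as ineffective.

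**Working it through.** **1. The plan's own figure.** For 83% vs 93%, two-sided alpha 0.05 (sidedness is not stated) and 80% power, the pooled two-proportion formula gives

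n = [1.96·√(2·0.88·0.12) + 0.842·√(0.83·0.17 + 0.93·0.07)]² / 0.10² ≈ 165 per arm.

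With three clusters per arm, the design effect is 1 + (380/3 − 1)·0.01 = 2.257, and 165 × 2.257 ≈ 372. That is within about 2% of the stated 380. Then 380/0.80 = 475 per arm, 950 in total. The stated figures reproduce.

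**2. Share past the schedule.** Assume ages are uniform within each one-year cohort of 150 per arm.

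- No delay: children of 15–24 months are 150 × 9/12 = 112.5 per arm, or 225 of 600 = 37.5% (24% of all 950 women).
- 3-month wait: children of 12 months or more at baseline, 150 of 300 per arm = 50%.
- 6-month wait: children of 9 months or more at baseline, (150 + 150 × 3/12)/300 = 187.5/300 = 62.5%.

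The lengths of the wait are assumptions.

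**3. Diluted effect.** With share f past the schedule and catch-up fraction c (the part of the effect these children still gain):

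difference = 10 × (1 − f + f·c) points.

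**4. Power.** Mothers with a child number 300 per arm, or 240 after 20% attrition. The design effect is 1 + (80 − 1)·0.01 = 1.79, so the effective n is 240/1.79 = 134.1. Using SE = √{[p₁(1−p₁) + p₂(1−p₂)]/134.1} and power = Φ(difference/SE − 1.96), with p₁ = 0.83:

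| Wait | f | c | Difference (points) | SE | Power |
|---|---|---|---|---|---|
| undiluted | 0 | – | 10 | 0.0392 | 72% |
| none | 37.5% | 0 | 6.25 | 0.0420 | 32% |
| none | 37.5% | 0.25 | 7.2 | 0.0414 | 41% |
| none | 37.5% | 0.50 | 8.1 | 0.0407 | 51% |
| none | 37.5% | 0.75 | 9.1 | 0.0400 | 62% |
| 3 months | 50% | 0 | 5.0 | 0.0429 | 21% |
| 6 months | 62.5% | 0 | 3.75 | 0.0437 | 14% |

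Pooled variances give 71% in the first row and leave the others within about one point. The undiluted 72% is below 80% because only 300 of the 475 women per arm have a child to score. That shortfall is separate from the dilution.

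**5. Restricted set.** With no delay, children under 15 months number 240 × 0.625 = 150 per arm. Their design effect is 1 + (50 − 1)·0.01 = 1.49, SE 0.0453, and power for 83% vs 93% is 60%. Adding births to the pregnant cohort (50 × 0.80 = 40 per arm) gives 190 per arm, design effect 1.623, SE 0.0420 and power 66%. These are best cases: they credit every such child with the full 10 points, although a 14-month-old's earlier doses are also settled before exposure.

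**The case against.** - **Catch-up.** A reader might infer that the outcome of the older children cannot change at all. The documents do not support that. The Introduction describes late vaccination, and the outcome is not limited to timely doses. An incompletely vaccinated child of 15–23 months may still complete the schedule. This stands, and it is why the effect is given as a range. It does not remove the dilution: timeliness is fixed, a child already complete cannot improve, and at 50% catch-up power is still 51% against 72%.
- **Another endpoint.** Under the newborn/live-birth rate the 1–2-year-olds are in neither numerator nor denominator, so they dilute nothing. This also stands. The point therefore concerns the panel-measured behaviour outcome, and the article states both without reconciling them.
- **Analysis set.** The article does not say that every enrolled child enters the comparison, and a fuller plan may restrict it. But the article itself sets the eligible ages, cohort sizes, survey timing and assumed effect, and these do not fit together.
- **Delay.** A reader might conclude that a wait of more than eight months puts end-line before the intervention, or that a year's wait leaves almost no power. Neither is supported: no length of wait is given, Research design and intervention allows a project extension so that all phases are completed, and the timeline figure is not available here.
- **Panel data.** In an analysis of change, a child with a fixed status adds little noise, so less power is lost than the end-line calculation shows. This stands. The article fixes neither form of analysis.

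**Conclusion.** The point holds for panel-measured immunization behaviour. With even ages, about 37.5% of the 600 children are past the schedule at baseline, and more by the time the intervention begins. The sample size ignores this. In an end-line comparison with no delay, the 10-point effect becomes 6.25 to 9.1 points as catch-up goes from none to 75%, and power at 240 per arm is about 32% to 62% instead of 72%. These figures rest on uniform ages, the assumed catch-up fractions, the plan's intraclass correlation and a normal approximation. They overstate the power loss if change from baseline is analysed. Intention in the 350 pregnant and prospective women is not affected.

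**What to change.** 1. Time end-line from the intervention start in each Palika, using the same date for the matched control ward, instead of about eight months after baseline.
2. Make the primary behaviour analysis the doses falling due between intervention start and end-line, in index children including births to women pregnant at baseline. Use dates of birth and of vaccination.
3. Report whole-panel completion, including catch-up, as secondary.
4. Reconcile the schedule-based outcome in mothers with the newborn/live-birth rate in the primary hypothesis, and state which is primary.
5. Restate the power for the restricted set, using the children still on schedule at the actual start date. Step 5 of the working gives upper limits for no delay: about 60% at 150 per arm, or 66% at 190.

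The intervention has not begun, so all of this is still possible. The cost is the collection of dates at end-line and fewer children in the primary behaviour analysis. Restriction does not restore 80% power, but it removes children with no dose left to fall due and aims the estimate at doses that the intervention can influence.

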### Participants

Eligible participants include mothers of children younger than two years, pregnant women, and prospective mothers. Prospective mothers are defined as women of reproductive age (18–30 years) who are not currently pregnant and do not have a child two years or younger, but express interest in having a child in the future. All participants must be 18 years or older and live within a one-kilometer radius of the health facility being studied. Potential participants will be excluded if they or a member of their family participated in any of the qualitative assessments.

